## **9.2 Data Sources**

Data for this study will be collected during a single visit previously scheduled for a routine follow-up of the RA disease.

Data for relevant medical history will be obtained from patient charts and/or documentation.

Local language patient questionnaires will be used for assessing various PROs, treatment expectations, patient needs and preferences. Questionnaires listed in Appendices indicate the version used for the validated translations; specific country versioning may vary depending on the translation process.

Health care resource utilization (HRU) will be assessed using patient documentation and patient interview.

Only data which are part of routine will be collected, except PRO questionnaires which are not deemed as an intervention and are inherent part of epidemiological studies.

### **9.3 Study Size**

Approximately 1500 RA patients will be included in the study. The study will include 100 sites in approximately 20 countries in Europe, America and Asia. Countries will recruit between 30 and 200 patients per country depending on the available patient population.

Current sample size calculation is based on information of global satisfaction measured by TSQM 1.4. It is also assumed that similar number of patients will be allocated to each country so that country level analyses will be explored, as well as overall population. Based on the literature [51, 83], it seems reasonable to assume that the standard deviation for the global satisfaction is about 20 with mean value range from 71 – 91.

A given sample size of N=1500 will be able to provide a 95% confidence interval (CI) with a half width of 1.01 in the overall study population.

For country specific analysis a sample of N=50 will be able to provide a 95% confidence interval (CI) with a half width of 5.68. . For country specific analysis a sample of N=30 – 200 will be able to provide a 95% confidence interval (CI) with a half width of 7.47 to 2.79.

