#### Comparative subgroup analysis

Subgroup analyses of all measures listed above are planned if there are sufficient patients in each subgroup listed below:

- According to the RA treatment
  - Patients currently treated with any synthetic DMARDs, tsDMARDs, csDMARDs, bDMARDs

- Patients with previous exposure to 1 bDMARD or 2 bDMARD
- Patients treated with orally or parenterally administered DMARD
- Patients treated with IV or SC administered DMARD
- Patients treated with DMARD monotherapy or combination therapy
- According disease activity (high or moderate)
- According to comorbidities
  - Patients with or without any kind of comorbidity
  - Patients with cardiovascular comorbidity

For continuous variables two sample t-tests or non-parametric tests will be used based on the data distribution; for categorical variables appropriate R×C tables will be constructed and Chi-square or exact Fisher tests will be used based on appropriate assumption.

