## **9.7 Limitations of the Research Methods**

Results cannot be generalized to the whole RA patient population universe due to enrolment of sub optimally controlled patients.

Results must be carefully interpreted due to the observational and cross-sectional nature of the study. Information about the percentage of screened patients that agreed to participate in this study will be not collected which may result in selection bias.

No hypothesis testing will be performed in the primary analysis. All other statistical tests performed in secondary analysis will be performed without formal hypothesis testing and resulting p-values will be interpreted in a descriptive manner.

Factors associated to cultural differences may influence the results per countries. Country specific sub analyses should be interpreted carefully due to low sample size.

There is a potential imbalance in the size in subgroups per treatment used or per presence of comorbidities. Comparisons between different subgroups should be interpreted in exploratory manner only. Confounding factors (e.g., disease duration and severity, level of treatment response, and number and type of co-morbidities) may not be equally distributed between the groups, which can lead to bias and subsequent misinterpretation.

No validated questionnaires will be used for assessing needs for PSP, treatment preferences and expectations. Adherence results will be based on self-reported outcomes that may be influenced by self-presentational and recall biases. Patients may overestimate the extent of their adherence. Past HRU is based on patient interviews in addition to patient charts, similarly might result in recall-biases.

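### The confidence-interval half-widths in Section 9.3 assume independent patients, although the 1500 patients are clustered in about 100 sites, so the stated precision is somewhat optimistic

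*Protocol*

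**What the plan says.** Section 9.3 takes its inputs from the global satisfaction score of the TSQM 1.4 and assumes that "the standard deviation for the global satisfaction is about 20 with mean value range from 71 – 91". From this it concludes: "A given sample size of N=1500 will be able to provide a 95% confidence interval (CI) with a half width of 1.01" in the overall population. It adds half-widths of 5.68 for a country of 50 patients and 7.47 to 2.79 for countries of 30 to 200.

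The same section describes the structure of the sample: "Approximately 1500 RA patients will be included in the study", and "The study will include 100 sites in approximately 20 countries in Europe, America and Asia". On country size it makes two statements: "Countries will recruit between 30 and 200 patients per country depending on the available patient population", and "It is also assumed that similar number of patients will be allocated to each country".

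Section 9.5.1 defines the primary endpoint for the full study population. Section 9.5.3 promises a 95% CI for continuous variables without naming a standard-error method. For subgroups it states: "For continuous variables two sample t-tests or non-parametric tests will be used based on the data distribution". It then names linear and logistic regression. Neither 9.3 nor 9.5.3 mentions site, an ICC or a design effect. Section 9.7 says that the primary analysis involves no hypothesis test and cautions: "Factors associated to cultural differences may influence the results per countries".

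**The concern.** A half-width computed as t × SD/√N is right only if patients are independent. Patients at one site share physicians, services and local practice. Section 9.1.5 itself says that satisfaction may depend on the services offered as well as on the effect of treatment. Some positive correlation within sites is therefore plausible, and any positive value makes the true half-width of the overall mean larger than 1.01.

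This matters because the primary analysis has no test: its CI is the only statement of uncertainty about the primary result. If the reported interval were computed in the same way as the planning figure, its coverage would fall below the nominal 95%.

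Separately, the assumption of similar numbers per country cannot stand beside a range in which the largest country may be 200/30 ≈ 6.7 times the smallest. Appendix 7 shows where it comes from: the sentence was carried over unchanged from a plan of about 100 patients per country.

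**Working it through.** **Inputs from Section 9.3:** N = 1500; SD = 20; 100 sites; about 20 countries; 30 to 200 patients per country. Hence 1500/100 = 15 patients per site and 100/20 = 5 sites per country on average.

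**Assumption (not in the protocol):** site ICC between 0.01 and 0.10.

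**Step 1: reproduce the stated figures.** Half-width = t(0.975, N−1) × 20/√N.

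| N | With t | With normal quantile | Stated |
|---|---|---|---|
| 1500 | 1.01 | 1.01 | 1.01 |
| 200 | 2.79 | 2.77 | 2.79 |
| 50 | 5.68 | 5.54 | 5.68 |
| 30 | 7.47 | 7.16 | 7.47 |

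The t formula gives all four figures exactly. The arithmetic is correct, and no variance inflation was applied.

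**Step 2: overall half-width with site clustering.** Design effect DE = 1 + (15 − 1) × ICC; half-width = 1.96 × 20 × √(DE/1500); effective N = 1500/DE. The last column is the coverage of an interval that ignores clustering, 2Φ(1.96/√DE) − 1.

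| Site ICC | DE | Half-width | Effective N | Coverage of unadjusted CI |
|---|---|---|---|---|
| 0.01 | 1.14 | 1.08 | 1316 | about 93% |
| 0.05 | 1.70 | 1.32 | 882 | about 87% |
| 0.10 | 2.40 | 1.57 | 625 | about 79% |

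The half-width is 7% to 55% wider than stated. The increase is at most about 0.56 points, or 0.56/20 ≈ 0.03 SD.

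**Step 3: country half-widths.** With five sites per country, m = N/5 and DE = 1 + (m − 1) × ICC. The t quantile on N − 1 degrees of freedom is kept.

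| N | m | DE at ICC 0.01 to 0.10 | Half-width | Stated |
|---|---|---|---|---|
| 30 | 6 | 1.05 to 1.50 | 7.65 to 9.15 | 7.47 |
| 50 | 10 | 1.09 to 1.90 | 5.93 to 7.83 | 5.68 |
| 200 | 40 | 1.39 to 4.90 | 3.29 to 6.17 | 2.79 |

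The relative loss is greatest in the largest countries, because five sites would then hold 40 patients each. A large country with more sites would lose less.

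**The case against.** The strongest reply is that little depends on the difference. The estimate is descriptive, no threshold or decision rests on it, and a half-width of 1.57 is still small against an SD of 20. That stands, and it limits the severity.

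A second reply is that the standard-error method belongs in the SAP, which is not shown. Section 9.5.3 promises a 95% CI and does not rule out a clustered one. That stands too: silence on the method is not a fault in itself. It does not rescue the half-widths in 9.3, which are fixed in the protocol and assume independence.

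A third reply is that the similar-numbers sentence does not enter the 1.01, and that 9.3 gives separate half-widths for 30, 50 and 200. Correct: it is stale wording that contradicts its own section, not the source of the precision problem.

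Three stronger readings are tempting, and the documents do not support them:

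- **Countries as a random sample.** With 75 patients per country and an assumed country ICC of 0.02 to 0.05, DE = 1 + 74 × ICC = 2.48 to 4.70, and the half-width would be about 1.6 to 2.2, more with unequal countries. But 9.5.1 targets the full study population, and nothing claims inference to countries outside the study. With country as a fixed stratum, between-country variance leaves the standard error. The caution in 9.7 about cultural differences does not change that.
- **All subgroup p-values and regression CIs too narrow.** This holds for covariates that vary mainly between sites. For those that vary within sites, a standard error that ignores site is too large, by roughly 1/√(1 − ICC), or about 5% at ICC 0.10. Disease activity and comorbidity plausibly vary within sites, so the direction is not established.
- **An equally weighted country mean as a requirement.** A pooled mean is what 9.5.1 specifies. Other weights would be a preference.

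**Conclusion.** The concern holds for the precision statement in 9.3. The four half-widths assume independent patients, and the sampling described beside them is clustered by site. The direction for the overall and country means is firm for any positive site ICC. The size is not, because it rests on an assumed ICC of 0.01 to 0.10 and on equal cluster sizes: about 1.08 to 1.57 overall instead of 1.01, and the ranges above for countries. The contradiction between similar country sizes and 30 to 200 patients is plain from the text.

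Severity is moderate. The study is not shown to be too small, and no conclusion is invalidated. What the plan lacks is a precision statement that fits its own design.

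**What to change.** - **Section 9.3, half-widths.** State them as ranges, with the site-level design effect and the assumed ICC: about 1.1 to 1.6 overall for a site ICC of 0.01 to 0.10, and about 7.7–9.2, 5.9–7.8 and 3.3–6.2 for countries of 30, 50 and 200 with five sites each. Update the country figures if the planned number of sites per country is known.
- **Section 9.3, allocation.** Delete the assumption of similar numbers per country and keep the 30 to 200 range.
- **Section 9.5.3, primary analysis.** Compute the 95% CI of the primary mean with site-clustered standard errors, or a random intercept for site, with country as a fixed stratum.
- **Section 9.5.3, subgroups and regressions.** Account for site there as well, since ignoring it can err in either direction. Model details can sit in the SAP.

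The cost is revised wording, some extra model specification across the comparisons, and a slightly less favourable stated precision. No additional patients or data are needed, provided that the site identifier is kept in the analysis data.

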### **9.4 Data Management**

Each center will document patient data in electronic case report forms (eCRF).

Diagnostic measures and observations routinely performed in patients included in this study will be entered by the researcher or staff under his/her supervision into the eCRFs provided by AbbVie, according to the protocol.

Only data specified in the protocol will be submitted to AbbVie.

The eCRF for investigators' use will be in English and will include the PROs and other questionnaires in English. Patients will receive questionnaires in their local language for self-administration. Results of patient completed questionnaires will be transcribed into the eCRF. Comorbidities will be coded according to up-to date version of MEDRA.

The investigator or delegated staff must complete the eCRFs. Neither AbbVie nor any agents acting on behalf of AbbVie may complete the eCRFs.

## **9.5 Data Analysis**

### **9.5.1 Primary variable**

The primary endpoint is the total satisfaction score as measured by TSQM 1.4 for the full study population.

### **9.5.2 Secondary variables**

The secondary variables are:

- Sociodemographic, medication and disease characteristics including RA disease activity scores of DAS28, CDAI/SDAI and proportion of patients with high or moderate disease activity as per DAS28, CDAI/ SDAI.
- Proportion of patients in which treating physician is going to switch the DMARD therapy. Proportion of different mode of action of next planned DMARD.
- Effectiveness, Side effects, Convenience, Global Satisfaction sub scores of TSQM 1.4.
- Total fatigue score measured by FACIT-F.
- RA functional capacity score of HAQ-DI.
- Duration and severity of morning stiffness scores.
- Worst reported pain score.
- Self-reported adherence score (VAS).
- Total score and individual components of WPAI-RA score (% Presenteeism, % Absenteeism, % Total work productivity impairment, % Total activity impairment).
- General quality of life Total score, PCS-score and MCS-score domains and scale scores of SF-36v2 for the full study population.
- Total Electronic health literacy scale score as measured by eHEALS for the full study population.

- Health resource utilization assessment scores in 12 months preceding the study inclusion for the full study population.
- Proportion of patients with different level of patients' need of PSP support for each question point as measured by AbbVie developed questionnaire
- Proportion of patients for each question point about patients' medication preferences as measured by AbbVie developed questionnaire
- Proportion of patients with different level of patients' treatment expectations for each question point as measured by AbbVie developed questionnaire

### 9.5.3 Data Analysis

Data from all clinical assessments of the patients will be summarized using summary statistics. Detailed statistical analysis plan (SAP) will be provided separately. Additional exploratory analyses may be added on a data driven basis and will be specified in SAP. Separate analysis is planned for each country based on the needs of the particular participating country.

Statistical analysis in general will include:

#### Descriptive statistics

Continuous variables will be summarized with number of patients, mean, standard deviation, median, 1st quartile, 3rd quartile, minimum and maximum values, and 95% confidence interval (CI) for mean or median (as appropriate). Categorical variables will be summarized with the number and proportion of patients in each category. Appropriate CI for proportion will be provided. Visualization tools will be used to present the distribution of data, if applicable.

#### Comparative subgroup analysis

Subgroup analyses of all measures listed above are planned if there are sufficient patients in each subgroup listed below:

- According to the RA treatment
  - Patients currently treated with any synthetic DMARDs, tsDMARDs, csDMARDs, bDMARDs

- Patients with previous exposure to 1 bDMARD or 2 bDMARD
- Patients treated with orally or parenterally administered DMARD
- Patients treated with IV or SC administered DMARD
- Patients treated with DMARD monotherapy or combination therapy
- According disease activity (high or moderate)
- According to comorbidities
  - Patients with or without any kind of comorbidity
  - Patients with cardiovascular comorbidity

For continuous variables two sample t-tests or non-parametric tests will be used based on the data distribution; for categorical variables appropriate R×C tables will be constructed and Chi-square or exact Fisher tests will be used based on appropriate assumption.

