### Patient Selection Criteria

Patient attending a routine visit, who fulfill ALL the following selection criteria, can be included:

- Male or female.
- Adult (aged  $\geq 18$  years).
- Has rheumatoid arthritis (RA), diagnosed either by the 1987-revised ACR classification criteria or by the 2010 ACR / EULAR classification criteria for RA.
- Currently treated with any kind of approved csDMARDs, tsDMARDs or bDMARDs.
- Has been exposed to no more than 2 bDMARDs at the time of the enrollment.
- His/her RA is sub optimally controlled, despite full tolerable dose of current DMARD therapy administered for  $\geq 3$  months.

- Definition of suboptimal disease control: having high or moderate disease activity (as defined by having DAS28 > 3.2) for at least 1 month but not more than for 4 months prior to the enrollment.
- Understands the language and willing/able to complete the patient reported outcome questionnaires.
- Does not participate in any kind of clinical study for RA.
- Has provided written authorization to the investigator to use and/or disclose personal and/or health data, or informed consent if requested by the local regulations.

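### Drug-class and route subgroups overlap as written, yet the protocol compares them with unadjusted tests that assume independent groups

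*Protocol*

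**What the plan says.** Under Comparative subgroup analysis (Protocol 9.5.3), all measures are to be analysed by subgroup where numbers allow. The drug-class entry reads "Patients currently treated with any synthetic DMARDs, tsDMARDs, csDMARDs, bDMARDs". The route entry reads "Patients treated with orally or parenterally administered DMARD". A further entry, "Patients treated with DMARD monotherapy or combination therapy", shows that patients on more than one DMARD are expected. The eligibility criterion in section 9.0, "Currently treated with any kind of approved csDMARDs, tsDMARDs or bDMARDs", does not restrict a patient to one class.

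The tests are fixed in the same place: "For continuous variables two sample t-tests or non-parametric tests will be used based on the data distribution". For categorical variables, R×C tables are built and "Chi-square or exact Fisher tests will be used based on appropriate assumption". Neither sentence mentions a covariate or a stratum, and no rule assigns a combination patient to a single group.

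Section 9.7 warns: "Confounding factors (e.g., disease duration and severity, level of treatment response, and number and type of co-morbidities) may not be equally distributed" between the groups, with possible bias. It also limits subgroup comparisons to an exploratory reading and p-values to a descriptive one. The last part of 9.5.3 plans multivariable linear or logistic models with stepwise selection, using demographic and clinical characteristics as predictors.

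**The concern.** A two-sample t-test, a rank test for separate groups, and a chi-square or Fisher test all assume that each patient is in one group only. The class and route lists do not ensure this. A patient on a parenteral bDMARD plus an oral csDMARD meets the definitions of bDMARD, csDMARD, any synthetic, oral and parenteral at once.

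Two things are at stake. First, a difference between overlapping groups is not the difference between treatments that a reader will take it for, and its standard error is wrong. Second, the comparison is crude although the protocol itself raises possible confounding and section 8.1 already collects relevant covariates. Section 7.2 makes evaluation by treatment modality and route a secondary objective, and section 6.2 expects differences across such subgroups to inform individual treatment choice. The estimates should therefore mean what they appear to mean, even as exploratory results.

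**Working it through.** **Plan's own figures.** No effect size, group size or overlap is stated for the subgroup comparison. The only related figures are the half-widths in section 9.3 (SD 20). With t(0.975, n−1) × 20/√n they reproduce: 1.01 (n=1500), 5.68 (n=50), 7.47 (n=30) and 2.79 (n=200). SD 20 is used below. All other inputs are labelled assumptions.

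**Step 1: does the overlap depend on which groups are paired?**
- Any synthetic against csDMARD or tsDMARD: one group is nested in the other.
- Any synthetic against bDMARD: a bDMARD plus csDMARD patient is in both.
- tsDMARD against csDMARD: a patient taking one of each is in both.
- Oral against parenteral: an oral plus parenteral patient is in both.

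None of these pairings avoids it.

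**Step 2: effect on the estimate.** Assume 750 oral only, 250 parenteral only and 500 both. Set the oral-only mean to 0, the parenteral-only mean to 5 and the mean for both to m.
- Oral group: n = 1250, mean 500m/1250 = 0.4m.
- Parenteral group: n = 750, mean (250×5 + 500m)/750 = 1.667 + 0.667m.
- Difference: 1.667 + 0.267m.

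With m midway (2.5) the difference is 2.33, which is 53% below 5. With m anywhere from 0 to 5 it runs from 1.67 to 3.00, an attenuation of 67% to 40%. With equal group sizes the shared patients cancel exactly, and a shared fraction s leaves 1 − s of the exclusive difference.

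**Step 3: effect on the standard error.** For group sizes n1 and n2 with c shared patients:
- Two-sample formula: 1/1250 + 1/750 = 0.00213; SE = 20 × √0.00213 = 0.92.
- Correct: subtract 2c/(n1·n2) = 2×500/(1250×750) = 0.00107, leaving 0.00107; SE = 20 × √0.00107 = 0.65.
- Ratio: √(0.00213/0.00107) = 1.41.

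**Step 4: true size of a nominal 5% test.** For equal groups sharing a fraction s, size = 2[1 − Φ(1.96/√(1−s))].

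| Shared fraction (assumed) | Formula | Simulation (200 per group, 10,000 runs) |
|---|---|---|
| 0 | 5.0% | 5.2% |
| 25% | 2.4% | 2.1% |
| 50% | 0.6% | 0.7% |
| 75% | 0.01% | 0.01% |

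Overlap makes the test conservative.

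**Step 5: confounding, separate from overlap.** Assume disjoint groups, no true treatment difference, and a confounder that is 10 to 30 percentage points more common in one group and worth 5 to 10 TSQM points. Bias = prevalence difference × effect, from 0.10×5 = 0.5 to 0.30×10 = 3.0 points. With SE = 20√(2/n), the probability of p < 0.05 is Φ(bias/SE − 1.96) + Φ(−bias/SE − 1.96): 6% to 32% with 200 per group (SE 2.00), and 7% to 66% with 500 per group (SE 1.26).

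**Step 6: what exclusive groups give.** In the Step 2 example with m = 2.5, oral only (750) against any parenteral (750) shows 3.33 with SE 20√(2/750) = 1.03, a ratio of 3.2. The overlapping comparison gives 2.33/0.92 = 2.5. The exclusive contrast is not 5 either, because combination patients count as parenteral, but it is well defined and its SE is right.

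**The case against.** The strongest reply is that 9.5.3 lists subgroups without saying which is tested against which, and defers detail to a separate SAP. Assigning combination patients is ordinary SAP content. This has force: the SAP may already define exclusive groups. But the protocol states both the groups and the tests, and the most favourable pairings still put combination patients on both sides.

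The protocol's own limits also stand. Subgroup results are exploratory, p-values are descriptive, and the multivariable models mean that adjustment is not absent. Those models, however, are predictive and stepwise. They are not presented as the adjusted subgroup comparison and do not force treatment group in.

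A reader might also infer more than the text supports:
- *That the protocol declares the groups confounded.* Section 9.7 says only that confounders may be unevenly distributed.
- *That observed differences will mainly reflect who receives which drug.* Nothing in the document shows this.
- *That overlap creates false differences.* In Step 4 it does the reverse.
- *That every split is affected.* High versus moderate activity, monotherapy versus combination, one versus two bDMARDs, and with versus without comorbidity are disjoint.
- *That no listed test handles more than two groups.* R×C tables do, and non-parametric tests can. The limit to two applies to the t-test.

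**Conclusion.** The point holds for the drug-class and route subgroups as the protocol text stands. Independent-sample tests are prescribed for groups that share patients, and no adjusted form of those comparisons is stated. The overlap pulls the estimated difference down whenever combination patients lie between the single-treatment groups, and makes the two-sample standard error too large. The amount depends on an overlap that the protocol does not give: under the assumed 750/250/500 split, 2.33 points instead of 5 (1.67 to 3.00 across the range for combination patients) and an SE 1.41 times too large. The confounding figures are also illustrations and rest on assumed imbalance.

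The primary endpoint, a descriptive satisfaction score in the full population, is unaffected. This change should be made because it is cheap and improves a secondary objective. It does not threaten the study's main result.

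**What to change.** In section 9.5.3, and in the SAP if it does not already do so:

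1. Define exclusive class groups: csDMARD only; tsDMARD with or without csDMARD; bDMARD with or without csDMARD. Define exclusive route groups: oral only; any SC without IV; any IV. With/without contrasts for each class are an acceptable alternative.
2. Keep the crude group summaries as description. Beside them, report the group difference with 95% CI from a linear or logistic model with treatment group forced in and covariates fixed in advance: age, sex, disease duration, comorbidities, prior bDMARD exposure and country.
3. Adjust for DAS28 only as a sensitivity analysis. It is measured at the single visit, after at least 3 months on current therapy, and may itself be a consequence of treatment.
4. Keep the exploratory reading required by section 9.7.

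The cost is a wording change and a little more programming. No new data are needed. Any synthetic remains as a descriptive summary but is no longer a comparison group.
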